**3. Figures**

a) AEDC:

- Graphs will be generated to describe a) the proportion of developmentally vulnerable children (<10^th^ centile ≥2 domains) and b) the proportion of children ‘on track’ amongst the overall cohort, natural conception, overall ART (assisted reproduction), IVF-only and ICSI-only cohorts

b) NAPLAN:

- Graphs will be generated to describe a) the proportion of children in the lowest band category and b) the proportion of children classified as ‘below minimum standard’ amongst the overall cohort, natural conception, overall ART (assisted reproduction), IVF-only and ICSI-only cohorts
- Represent as box and whisker plot of test scores for each study population
- Use of z-scores standardised by year of test and year level – we will use whole of Australia national standards

**STATISTICAL ANALYSIS**

**PART ONE – AEDC**

**Causal research question:** What is the causal effect of conception via IVF compared to natural conception on AEDC-defined outcomes for children?

**Exposure**: IVF conception.

**Primary outcome:** A score of <10^th^ centile in “2 or more” domains (Binary yes/no).

**Secondary outcomes:** A score in the lowest decile in each domain: 1) physical health and wellbeing, 2) social competence, 3) emotional maturity, 4) language and cognitive skills, and 5) communication skills and general knowledge.

**Inclusion criteria:** Children born in the study time period.

**Exclusion criteria:** Multiple pregnancies, known congential anomaly.

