**BACKGROUND**

**In-Vitro Fertilisation (IVF) is common.** 5% of Australian births are now conceived by IVF. It is well established that pregnancy following IVF is associated with higher risk of maternal and perinatal complications than pregnancy where conception occurs naturally. There is emerging epidemiological evidence suggesting that Intra-Cytoplasmic Sperm Injection (ICSI) may be associated with an increased risk of congenital abnormalities, Autism Spectrum Disorder and other developmental abnormalities compared to (standard) IVF or natural conception. Analysis of existing data has, however, generated results on the risk of these adverse outcomes that are not consistent across studies.

**There are currently few published studies looking at population-wide school-age education and developmental outcomes among children following IVF conception with appropriate comparison between difficerent types of assisted reproductive technology (ART) and a control group representing natural conception (NC).** We will use record-linkage of existing administrative datasets to investigate the evidence of a causal relationship between relatively rare exposure of IVF (compared to natural conception, or ICSI compared to IVF) and the developmental and educational outcomes of primary school-aged children. Outcomes measures of primary interest are achievement assessed using the Australian Early Developmental Census (AEDC) and National Assessment, Literacy and Numeracy (NAPLAN) metrics.

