**CAUSAL RESEARCH QUESTION**

***What are the causal effects of Invitro Ferilization (IVF) v Natural Conception (NC) and IVF with Intracytoplasmic Sperm Injection (ICSI) v conventional IVF on the school-age developmental and educational outcomes for children?***

P – All Mothers (and their babies) who gave birth in Victoria during the period 2005-2018

*Note: we intend to consider mothers, fathers and children part of the target population even if we know that they do not have outcomes data available (e.g. AEDC)*

I – Conception via (i) any IVF; (ii) IVF with ICSI.

C – Conception via (i) natural conception (excluding ovulation induction (OI) and intra-uterine insemination (IUI)); (ii) conventional IVF.

O – Developmental and educational outcomes – AEDC and NAPLAN (Grade 3) scores.

T – The nominal age at which children are measured for AEDC (foundation school year: 4-6 years of age) and NAPLAN (school year level 3: 7-9years of age) are typically measured.

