**Causal Inference methodology**

| *The steps to* ***causal inference****:*   1. *Think carefully about the precise nature of the causal question to be addressed, usually around a currently humanly feasible intervention that we wish to apply to the whole of the target population, and compare the outcome (averaged over the whole of the target population) to the corresponding average outcome that occurs when no one in the target population gets the intervention;* 2. *Convert the causal question in Step 1 to a precise quantity to be estimated (a causal estimand), usually using the notation of the potential outcomes approach to causal inference.* 3. *At least state and, if possible, be rigorous and honest about the the assumptions (e.g. consistency, conditional exchangeability, positivity) under which the estimand in Step 2 can be identified from the data at hand;* 4. *Find (or develop!) estimation strategies (i.e. statistical methods) that are valid under the assumptions in Step 3. Apply these to the data in Step 3;* 5. *Use statistical tools to assess quantitatively the sensitivity of the results to plausible departures from the assumptions in Step 3.* |
| --- |

1. Develop a causal model using directed acyclic graphs (DAGs) to both identify and summarize causal pathways.
   1. Potential confounders – demographic and perinatal – will be determined by a quorum of specialists with expert knowledge:
      1. Childs age at assessment (continuous)
      2. Gender (binary)
      3. Birthweight centile (continuous or binary, eg < 10^th^ centile)
      4. Gestational age of delivery (continuous)
      5. Mode of delivery (categorical)
      6. Level of maternal education (categorical)
      7. Maternal age (continuous)
      8. SEIFA quintile (categorical)
      9. LBOTE (binary)
      10. ATSI (binary)

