*The* ***primary analysis*** *will focus on the* ***total effect*** *of IVF conception adjusted for common cause confounders. Part 4 outlines the proposed mediation analysis where* ***direct*** *and* ***indirect*** *(mediated) pathways (eg via prematurity) may be further investigated.*

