**PART THREE – ICSI ANALYSIS**

ICSI forms an important and growing proportion of IVF technique. Outcomes amongst this sub-population will be explored separately and subsequent to the analyses in Part One and Two.

**Causal research question:** What is the causal effect of conception via ICSI compared to non-ICSI (conventional) IVF compared to natural conception on AEDC and NAPLAN outcomes for children?

**Exposure**: IVF with ICSI

**Primary outcome: *AEDC*** A score of <10^th^ centile in “2 or more” domains (Binary yes/no). ***NAPLAN***: Z score to be generated from our cohort using published mean and SD for national-scaled scores.

**Secondary outcomes:** ***AEDC*** A score in the lowest decile in each domain: 1) physical health and wellbeing, 2) social competence, 3) emotional maturity, 4) language and cognitive skills, and 5) communication skills and general knowledge. ***NAPLAN:*** Above or below minimum standard for each of the four domains (binary).

**Inclusion criteria:** Children born in the study time period.

**Exclusion criteria:** Multiple pregnancies, known congential anomaly.

*If there* ***ARE*** *differences in developmental and educational outcomes between ICSI and conventional IVF cohorts, we propose that this will be considered and reported as a primary finding since we have stated this sequential planned analysis a priori.*

The same methodology of causal inference, detailed in Part One and Two, will be employed for this analysis.

*Again, this analysis will focus on the* ***total effect*** *of ICSI conception adjusted for common cause confounders.*

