**Proposed Causal Mediation Analyses**

*The relationships between variables represented in the DAG are complex, with mutltiple interacting pathways.*

Untangling this classification, we would be safe adjusting all analyses for **SEIFA**, **LBOTE**, **maternal** **education**, **ATSI**, **maternal age**, **male** and **female sub-fertility**, and **multiple pregnancy**. One could also adjust for obesity, but with adjustment for SEIFA, LBOTE, Maternal education, ATSI and female sub-fertility there are no remaining open back-door paths from exposure (IVF) to outcome (NAPLAN) that contain obesity.

That leaves four mediators: **caesarean Section (CS)**, **small for gestational Age (SGA)**, **prematurity (PTB)**, and **developemental delay**.

**Caesarean section** is effected by both prematurity and SGA thus is on the following mediated paths:

(1) IVF 🡪 SGA 🡪 🡪 CS 🡪 NAPLAN;

(2) IVF 🡪 Prematurity 🡪 C/S 🡪 NAPLAN; and

(3) IVF 🡪 C/S 🡪 NAPLAN.

**Proposed analysis:** Dependent on the total effect of IVF 🡪 C/S 🡪 NAPLAN (expected to be small) in our cohort we could consider **excluding** this mediator in the analysis.

**DevelopDelay** is on three mediated paths:

(1) IVF 🡪 SGA 🡪 Prematurity 🡪 DevelopDelay 🡪 NAPLAN;

(2) IVF 🡪 Prematurity 🡪 DevelopDelay 🡪 NAPLAN; and

(3) IVF 🡪 DevelopDelay 🡪 NAPLAN.

Even with all of these variables measured, these path-specific mediated effects cannot be estimated individually.

**Proposed analysis:** **excluding** DevelopDelay as a variable in the analysis allows its mediated effect to be absorbed through the other paths, that is, through the effects mediated by LBW and prematurity.

That leaves just **SGA** and **PTB** where the former often directly causes the latter.

**Proposed analysis:** Consider one or other of these mediators in a causal mediation analysis, or at least perform separate mediation analyses one mediator at a time. It would be possible to estimate the causal effect of IVF on NAPLAN mediated by Prematurity **not including** any effect through SGA and, in the same analysis, estimate the causal effect of IVF on NAPLAN mediated by SGA but it’s **not possible to separate** the causal effect of IVF on NAPLAN mediated effect SGA that **does** and **does not** go through **prematurity**, only the combined effect of the two mediated causal paths IVF 🡪 SGA 🡪 Prematurity 🡪 NAPLAN and IVF 🡪 SGA 🡪 NAPLAN.

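### Parts One to Three claim a total effect in all births, but their exclusions limit them to singletons without a known congenital anomaly

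*SAP*

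**What the plan says.** The Causal Research Question section of the SAP sets the population as "All Mothers (and their babies) who gave birth in Victoria during the period 2005-2018". It keeps families "part of the target population even if we know that they do not have outcomes data available". The first step in the Causal Inference methodology box says that the outcome under each condition is "averaged over the whole of the target population".

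The closing note of Part One states that the primary analysis targets the total effect "of IVF conception adjusted for common cause confounders". Part Two repeats this for NAPLAN, and Part Three says the same for the total effect "of ICSI conception adjusted for common cause confounders".

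The exclusion criteria are identical in Parts One, Two and Three: "Multiple pregnancies, known congential anomaly".

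The Background says that ICSI "may be associated with an increased risk of congenital abnormalities, Autism Spectrum Disorder and other developmental abnormalities". It calls this evidence emerging and says that results differ between studies.

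Part Four, under Proposed Causal Mediation Analyses, says "Untangling this classification, we would be safe adjusting all analyses for" a list of variables that ends with multiple pregnancy. The last line of Part Four expects the mediation work to be done as a separate project.

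**The concern.** A total effect of conception mode includes everything that follows from it, whatever the pathway. Plurality and congenital anomaly are settled at or after conception. Restricting the analysis on them removes whatever part of the effect passes through them, and the restricted group is no longer the population that the SAP names.

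The stake is interpretation. A null or small difference could be reported as the total effect of IVF or ICSI on Victorian children when children with anomalies and children from multiple births were never analysed. For anomaly, the SAP's own motivation raises the pathway that the exclusion closes.

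**Working it through.** The SAP states no figure on this point that could be reproduced, so the main check is a comparison of its sections.

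**1. Population, effect and analysis set**

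| Element | Where | Content |
|---|---|---|
| Population | Causal Research Question | All births 2005–2018; no limit on plurality or anomaly |
| Averaging | Causal Inference methodology, step 1 | Whole target population |
| Effect | Parts One, Two and Three | Total effect |
| Analysis set | Parts One, Two and Three | Singletons without a known anomaly |

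The last row does not match the first three. The visible text gives no reason for the exclusions, no restated estimand and no analysis that includes the excluded children. Step 5 of the same methodology box does call for sensitivity assessment.

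**2. Role of the two variables.** The SAP adopts a definition of confounding as a cause shared by exposure and outcome. Something fixed at or after conception cannot be a cause of the mode of conception, so neither variable qualifies. Part Four treats other downstream events (caesarean section, low birth weight, prematurity) as mediators. Its written classification places neither plurality nor anomaly anywhere.

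**3. Size of the omitted part (illustration; every rate is assumed).** Omitted part = (rate of the condition in exposed − rate in unexposed) × effect of the condition on the outcome.

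Assumptions: multiples 1.5% after natural conception v 3%, 5%, 10% or 20% after IVF; anomaly 3% v 3.5%, 4.5% or 6%; NAPLAN loss per affected child 0.1, 0.2, 0.4 or 0.8 SD; extra AEDC risk per affected child 3, 10 or 20 points.

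| Condition | Outcome | Smallest | Largest |
|---|---|---|---|
| Multiples | NAPLAN | 0.015 × 0.1 = 0.0015 SD | 0.185 × 0.8 = 0.148 SD |
| Multiples | AEDC | 0.015 × 3 = 0.045 points | 0.185 × 20 = 3.7 points |
| Anomaly | NAPLAN | 0.005 × 0.1 = 0.0005 SD | 0.03 × 0.8 = 0.024 SD |
| Anomaly | AEDC | 0.005 × 3 = 0.015 points | 0.03 × 20 = 0.6 points |

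The smallest NAPLAN difference that the SAP calls meaningful is 0.1 SD. Of the 28 NAPLAN combinations (16 for multiples, 12 for anomaly), only the 0.148 SD one exceeds it. At 5% multiples the range is 0.035 × 0.1 = 0.0035 to 0.035 × 0.8 = 0.028 SD. Of the 21 AEDC combinations, three exceed 1 point (1.7, 1.85 and 3.7), all for multiples at 10% or 20%.

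**4. Selection bias (illustration).** Suppose an unmeasured factor with 20% prevalence triples the risk of exclusion and lowers the score by 0.2 or 0.4 SD, and that baseline exclusion is 3%. If exposure multiplies the exclusion risk by 4, the factor's prevalence among retained exposed children is 0.2 × 0.64 / (0.2 × 0.64 + 0.8 × 0.88) = 0.154. Among retained unexposed children it is 0.2 × 0.91 / (0.2 × 0.91 + 0.8 × 0.97) = 0.190. With the 0.4 SD effect, the bias is (0.190 − 0.154) × 0.4 = 0.014 SD. With a multiplier of 1.5 and an effect of 0.2 SD it is 0.001 SD.

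**5. Part Four list.** After the exclusion, multiple pregnancy takes one value for every child. It cannot be adjusted for, and by step 2 it is not a confounder.

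**The case against.** The strongest reply is that restricting to singletons without anomaly is a legitimate and explicit choice, stated beside the question in every part, and that only a label needs correcting. That largely stands. The fault lies in the mismatch with the stated population and effect. Making an analysis that retains anomalies primary is an option that the sponsor may reasonably decline.

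Size is also a fair objection. A rough AEDC half-width for IVF v natural conception is 0.53 points: 1.96 × √(0.05 × 0.95 / 6,429). Here 6,429 = 30,000 × 3/14, which treats the SAP's approximate cycle count as children spread evenly over 14 birth years, with three AEDC rounds and full linkage. The 5% risk is assumed, and only the IVF arm's variance is counted. The anomaly part falls below this in all but its most extreme combination (0.6 points). The omitted part may therefore be hard to see in the data, but a wider interval does not change which children the estimate describes.

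A reader might infer that the exclusions bias results toward no harm. That needs the exposure to raise these conditions and the conditions to worsen outcomes. The SAP gives no figures for either, calls the anomaly evidence inconsistent, and never says that IVF raises multiple births. A reader might also infer that ICSI v conventional IVF suffers most, but the Background compares ICSI with both IVF and natural conception and does not single out that contrast. Nor are all the children of concern removed: the Background also names autism and other developmental abnormalities, which no exclusion criterion mentions.

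The Part Four wording might be read as a serious contradiction. It is conditional, belongs to deferred work, and concerns a variable that would be constant, so it alters no estimate in Parts One to Three. The flow chart and causal diagram are not shown and may place these variables, but they could not reconcile the written exclusions with the written population.

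**Conclusion.** The point holds as a mismatch between the stated estimand and the analysis set. Parts One to Three will estimate an effect among singletons without a known anomaly, which is not the total effect in all Victorian births. Any effect through plurality or anomaly is omitted, and selection bias is possible.

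The mismatch follows from the SAP's own text and from the timing of the two conditions. It needs no assumed rate. Size and direction do need assumed rates. In the ranges tried, the omitted part is mostly minor on NAPLAN and could reach a few percentage points on AEDC only with high multiple-birth rates and large effects per child. The selection component was 0.001 to 0.014 SD. The Part Four entry is a secondary tidying point.

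**What to change.** - In Parts One to Three, restate the population and estimand as the effect among singleton births without known congenital anomaly, and do not describe it as the total effect in all births.
- Add two sensitivity analyses: (a) retain children with congenital anomaly; (b) also include multiples, with clustering by mother. Adjust for neither plurality nor anomaly in either run. Making the anomaly-inclusive analysis primary is optional.
- Remove multiple pregnancy from the adjustment list in Part Four.

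The cost is SAP wording, two extra runs and a narrower stated conclusion.

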**Causal Inference methodology**

| *The steps to* ***causal inference****:*   1. *Think carefully about the precise nature of the causal question to be addressed, usually around a currently humanly feasible intervention that we wish to apply to the whole of the target population, and compare the outcome (averaged over the whole of the target population) to the corresponding average outcome that occurs when no one in the target population gets the intervention;* 2. *Convert the causal question in Step 1 to a precise quantity to be estimated (a causal estimand), usually using the notation of the potential outcomes approach to causal inference.* 3. *At least state and, if possible, be rigorous and honest about the the assumptions (e.g. consistency, conditional exchangeability, positivity) under which the estimand in Step 2 can be identified from the data at hand;* 4. *Find (or develop!) estimation strategies (i.e. statistical methods) that are valid under the assumptions in Step 3. Apply these to the data in Step 3;* 5. *Use statistical tools to assess quantitatively the sensitivity of the results to plausible departures from the assumptions in Step 3.* |
| --- |

1. Develop a causal model using directed acyclic graphs (DAGs) to both identify and summarize causal pathways.
   1. Potential confounders – demographic and perinatal – will be determined by a quorum of specialists with expert knowledge:
      1. Childs age at assessment (continuous)
      2. Gender (binary)
      3. Birthweight centile (continuous or binary, eg < 10^th^ centile)
      4. Gestational age of delivery (continuous)
      5. Mode of delivery (categorical)
      6. Level of maternal education (categorical)
      7. Maternal age (continuous)
      8. SEIFA quintile (categorical)
      9. LBOTE (binary)
      10. ATSI (binary)

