      11. BMI
      12. Other potential confounders:
          1. Parents overseas born
          2. Occupation of both parents
          3. Second parent level of education
          4. Parity

The list of covariates to be included in the propensity score model will be finalised after consideration of potential open backdoor causal paths and conditioning effects of collider nodes. The list above will be used as start. Distinction will be made between the standard epidemiological definition of a confounder and the causal pathway definition.

**Causal pathway and confounding** *(excerpt from Causal Inference , What if. M Hernan & J Robins p85:* [*https://www.hsph.harvard.edu/miguel-hernan/causal-*](https://www.hsph.harvard.edu/miguel-hernan/causal-) *inference-book/*)

“..the bias has the same structure: it is due to the presence of a cause (known covariate L or unknown covariare U) that is shared by the treatment A and the outcome Y, which results in an open backdoor path between A and Y. We refer to the bias caused by shared causes of treatment and outcome as confounding,…”

**These potential confounders (PS_covariates) will then be used in the construction of a propensity score model for exposure assignment (vide infra).**

1. Handling of missing data using Multiple Imputation

a. Consideration of missing data will be confined to all the covariates identified for the construction of a (propensity score) model of the exposure status. When imputing these missing covariate values the imputation model will include include: the outcome; all covariates identified for inclusion in the propensity score model with any transformations and interaction terms where appropriate; as well as additional auxillary covariates* from the BOS database/NAPLAN/AEDC databases. *These co-variates will be selected once the data are available for review.

b. Multiple imputation will be performed using either Multiple Imputation by Chained Equations (MICE) and/or Missing Covariate Indicator Method (MCIM) and the imputed datsets will then be used for propensity score construction. Subjects with missingness greater than 50% of PS_covariates will be excluded from analysis, this proportion will be assessed and if substantial, may result in changes to the PS_covariate list used for ongoing analysis.

c Diagnostics will then be performed to assess the quality of the imputed datasets.

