d. For each of these imputed datasets Inverse Probability Weights (IPW, vide infra) will be calculated and used in weighted regression analyses. For each outcome metric, average point estimates and standard errors (95% CI) appropriately adjusted, given the imputation framework, will be obtained. The number of imputed datasets will be set at a minimum of 20 with the number increased to equal to the highest percentage of missingness in the raw PS_covariate list (ceiling of 50% by design). Details of imputation and assessment of adequacy will be formally presented.

1. Development of Inverse Probability Weights.

a) For each imputed dataset, logistic regression with robust standard errors will be performed for the binary exposure against all the PS_covariates. Inverse probability weights will be calculated for each individual given their exposure and these will be used to weight the adjusted regression model.

b) For each imputed dataset the distribution of IPW by exposure status will be examined to ensure: (i) that there is common support (overlap) of the distributions adequacy of adjustment; and (ii) that the weighting was effective in equalizing the covariate distributions in the ‘pseudopopulation’. This will be performed using standardized difference (StD) constructed from the imputed mean minus the raw data mean for all PS_covariate, with an StD of less than 10% being considered adequate. Forrest plots comparing unadjusted and adjusted covariate distributions will also be performed.

1. Regression modelling
   1. All causal regression modelling wil be performed within the multiple imputation frame-work using the IPW propensity score-based weights.
   2. The outcome metric is considered to be absolute risk difference between IVF exposure groups. This will be performed using either generalized linear modelling with Poisson link to directly generate Relative Risks or via logistic regression modelling.
   3. Software: analysis will be performed using Stata v16 (StataCorp. 2019. *Stata Statistical Software: Release 16*. College Station, TX: StataCorp LLC. Causal inference will be performed using teffects commands (Treatment-effects estimation for observational data - see TE -teffects) run within within Stata’s multiple imputation suite.

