**Types of nodes (variables) in the above DAG**

**Common-cause confounders of the causal effect of the primary exposure (IVF) on the primary outcome (NAPLAN) [arrows from these variables to both IVF and NAPLAN]:** SEIFA, LBOTE, Maternal education, ATSI. Adjust all analyses (via IPW) for these as potential confounders.

**Mediators of the causal effect of** **the causal effect of the primary exposure (IVF) on the primary outcome (NAPLAN) [arrow from IVF to this variable, and then from this variable to NAPLAN, so they are “on the causal pathway”]:** CS, LBW, Prematurity (PTB), DevelopDelay.

**Variables that are common-cause confounders of the causal effect of the exposure (IVF) on one or more mediators:** Male SubFert and Female SubFert (confounds IVF and Prematurity), Maternal age (confounds IVF and all of CS, LBW and Prematurity).

**Variables that are common-cause confounders of mediators or causes of mediators (but are not mediators themselves):** Obesity, Maternal age.

**Mediators that common-cause confound the causal effect of another mediator on the outcome (NAPLAN) and are therefore “Exposure-Induced Mediator-Outcome Confounders” (EIMOC’s):** LBW (on Prematurity), Prematurity (on DevelopDelay).

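### The starting propensity-score list contains birthweight centile, gestational age and mode of delivery, which Part Four classes as mediators; if carried forward unchanged, the analyses would not estimate the stated total effect

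*SAP*

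**What the plan says.** Step 1 of the Causal Inference methodology in Part One lists potential confounders. Items 3 to 5 are "Birthweight centile (continuous or binary, eg < 10^th^ centile"), "Gestational age of delivery (continuous") and "Mode of delivery (categorical").

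After the list, the SAP says that it is a starting point, to be settled by looking at back-door paths and colliders, and that two definitions of a confounder will be told apart. It then quotes a causal-inference textbook, which defines confounding by a cause shared by treatment and outcome. The next statement is in bold: "These potential confounders (PS_covariates) will then be used in the construction of a propensity score model for exposure assignment". Under Development of Inverse Probability Weights, "logistic regression with robust standard errors will be performed for the binary exposure against all the PS_covariates".

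The closing note of Part One defines the primary analysis as the total effect "of IVF conception adjusted for common cause confounders" and gives prematurity as an example of a mediated pathway. Part Two repeats that note and takes over steps 1 to 3 unchanged. Part Three uses the same methodology and also targets the total effect.

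Part Four, Types of nodes, lists the mediators of IVF on NAPLAN as "CS, LBW, Prematurity (PTB), DevelopDelay". Proposed Causal Mediation Analyses repeats the list with SGA in place of low birthweight. It gives a set that is safe for all analyses: SEIFA, LBOTE, maternal education, ATSI, maternal age, male and female subfertility, and multiple pregnancy. None of the three birth variables is in it.

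**The concern.** Birthweight centile, gestational age and mode of delivery are all determined after conception, so they cannot be causes of IVF. They can be consequences of it. Weighting on a consequence of exposure makes the exposed and unexposed groups alike on it, and so takes out whatever part of the effect runs through it. What is left is closer to a direct effect than to the total effect that the SAP names as primary.

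The list and Part Four therefore lead to two different quantities. An analyst who follows the step 1 list and one who follows Part Four would both be able to say that they had followed the plan. Because Parts Two and Three inherit the method, this touches every primary analysis in the document.

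**Working it through.** **Setting the passages side by side.** The SAP states no figure on this point, so the main check is of consistency.

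| Variable in the step 1 list | Construct in Part Four | Class in Part Four | In Part Four's safe set? |
| --- | --- | --- | --- |
| Birthweight centile (item 3) | LBW / SGA | Mediator | No |
| Gestational age (item 4) | Prematurity | Mediator | No |
| Mode of delivery (item 5) | Caesarean section | Mediator | No |

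The labels differ, but each pair measures the same thing.

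**Does any step take the three variables out?**

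1. Finalising the list: the stated considerations are back-door paths and colliders. Removing mediators, or variables affected by exposure, is not named.
2. Missing data: the list may change if many subjects lack more than half of the covariates. That is unrelated to mediation.
3. Weighting: exposure is modelled on all the covariates, with no exception.
4. Balance check: weighting is meant to equalise every listed covariate, with a standardised difference below 10% as the criterion. With gestational age on the list, equal gestational age in the two weighted groups would count as success, so the diagnostic would not reveal the problem.

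**Illustration of direction (all inputs assumed, none from the SAP).** A simulation used n = 1,000,000, about 3% exposed, one confounder C, one mediator M and a continuous outcome. The effect of exposure on M was -0.2 or -0.4, of M on outcome 0.1 or 0.2, and the direct effect 0 or -0.05. True total = direct + (exposure on M) × (M on outcome), which runs from 0 + (-0.2 × 0.1) = -0.02 to -0.05 + (-0.4 × 0.2) = -0.13.

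- Propensity model with C only: the estimate was within 0.024 of the true total in all 16 settings.
- Model with C and M, no unmeasured cause of M and outcome (8 settings): the estimate was within 0.015 of the direct effect. For example, with a true total of -0.080 and a direct effect of 0, C only gave -0.085, and C with M gave -0.010.
- Model with C and M, plus an assumed unmeasured cause of both M and outcome (8 settings): the estimate was positive in 7 of 8, although every true total was negative.

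**Illustration of size, prematurity path only (inputs again assumed).** Effect removed = (difference in preterm risk) × (effect of preterm birth on outcome).

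- AEDC: a preterm difference of 2 to 6 points and an effect of 3 to 10 points give 0.02 × 0.03 = 0.0006 to 0.06 × 0.10 = 0.006, or 0.06 to 0.6 percentage points.
- NAPLAN: an effect of 0.1 to 0.4 SD gives 0.02 × 0.1 = 0.002 to 0.06 × 0.4 = 0.024 SD. The upper end is 0.024 / 0.1 = 24% of the 0.1 SD that Part Two calls mild.

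Paths through growth and mode of delivery are not included.

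**The case against.** The strongest defence is that the SAP's intent is right and the list is only a draft. It says that the list will be finalised, and the textbook definition that it quotes requires a cause shared by exposure and outcome, which none of the three variables can be. The total-effect statements speak only of common-cause confounders, and Part Four gives a set without the birth variables for all analyses. The bold sentence can be read as referring to the finalised list. All of this stands, and it is why the point is conditional. It does not dispose of it. Part Four already settles the status of these variables in the same document, yet the list was not brought into line, and nothing says in so many words that mediators come out.

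Part Four is also written for IVF and NAPLAN. However, the Part One note names prematurity as a mediated path for AEDC, and for ICSI the three variables equally follow conception.

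A reader might infer three stronger things, which the document does not support:

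- That the SAP commits to adjusting for mediators. It does not, because the list is provisional.
- That the SAP's own diagram shows collider bias through subfertility. Part Four says that subfertility confounds IVF and prematurity. Bias by that route needs a further path from subfertility to the outcome, or another unmeasured cause of mediator and outcome. The text states no such path for subfertility, and the figure is not available. The sign changes in the simulation come from a shared cause that was assumed.
- That a large share of the effect would be lost. Any such share depends on an assumed total effect, and the NAPLAN figures for prematurity alone are small.

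**Conclusion.** The inconsistency is real and concerns what the primary analysis estimates. If items 3 to 5 go into the propensity model as listed, the weighted analyses in Parts One to Three block pathways that Part Four calls mediated, and they do not estimate the stated total effect. This rests on two things: that the list is carried forward unchanged, and that the SAP's own classification of mediators is right.

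The size of the bias cannot be derived from the document. The ranges shown are illustrations for one path under assumed inputs. The case rests on the wrong estimand, not on a demonstrated large bias. It should be settled before the propensity model is fitted, because the planned balance check would not bring it to light.

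**What to change.** In the SAP, for the total-effect analyses in Parts One to Three:

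1. Delete birthweight centile, gestational age and mode of delivery from the propensity-score covariates.
2. State that no variable that can be affected by mode of conception, including any that Part Four classes as a mediator, enters the propensity score.
3. Reconcile the step 1 list with Part Four and print one final set. Maternal age is in the list and in Part Four's safe set, but not among the common-cause confounders under Types of nodes. Male and female subfertility are in the safe set but not in the list, and should be included where recorded.

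Child's sex and age at assessment need not be dropped by this change, since Part Four classes neither as a mediator. The three deleted variables may stay in the imputation model as auxiliaries and be used in the separate mediation project.

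The cost is SAP wording only. No extra data are needed.
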